##### Self-Esteem

The benefits of foot reflexology on the level of self-esteem will be assessed at the end-of-study visit using the Body Image Questionnaire (BIQ) [33], which measures body image at a given time. The analysis of the BIQ takes into account the level of self-esteem assessed at the baseline using the Rosenberg scale [34].

#### Adverse Events

All adverse events are collected during this study and the assessment of causality with foot reflexology is at the physician's discretion.

### Sample Size

In a study reported by Billhult et al [35], the mean improvement for CINV (measured using a VAS) was 49.5% in the placebo group, and 73.5% in the massage group (with a common standard deviation of 32.2%). Assuming these same hypotheses, for a two-sided risk of 5%, it is necessary to include 40 patients per group to demonstrate a statistically significant difference between the two groups with a power of 90%.

### Type of Statistical Analysis Used

Study data are entered into a password-protected Excel spreadsheet (version 14.0, Microsoft Corp) accessible only to the project manager. Quantitative data will be described for the entire population, using the following descriptive statistics: the number, the number of missing values, the mean, the standard deviation, the median, the interquartile range, and the range. Qualitative variables will be summarized for the entire population using the following descriptive statistics: the frequency and percentage for each category of the variable and the missing values (missing values will be counted but are not included in the denominator of the calculation of frequencies).

For the primary endpoint, comparison of the relative change in the VAS between the two groups will be performed using a linear model adjusted on the type of cancer (digestive system or lung) and the presence of metastases (randomization stratification factors). This model allows the estimation of the difference in mean relative variation of VAS between the two groups, adjusted on potential confounding factors, with a 95% confidence interval. The VAS score may be transformed satisfy the assumptions of the linear model. If the assumptions of the model cannot be verified, the comparison between the two groups will be done using the van Elteren test. Specific estimates of the difference in relative VAS variation between the groups will be provided for both types of cancer, and by metastatic status.

The comparison of the frequency of episodes of CINV between chemotherapy cycles between the two groups will be performed using a mixed effects Poisson model, integrating the number of intercycle days as offset. The model will consider the intervention group and stratification criteria as fixed effects, and will incorporate one random intercept per patient.

The proportion of chemotherapy cycles in which the patient took at least one antiemetic drug will be compared between the two groups using a mixed effect logistic regression model. The model will consider the intervention arm and stratification criteria as fixed effects, and will incorporate one random intercept per patient.

The comparison of quality of life and anxiety between the two groups will be done using a Wilcoxon test.

The comparison of self-image between the two groups will be done using a linear model adjusted on the baseline self-esteem evaluated with the Rosenberg scale. A possible transformation of the BIQ score will performed to satisfy the assumptions of the linear model.

The analysis will be performed according to the intention-to-treat principle, considering all patients that completed the endpoint evaluation in the group that was allocated to them by the randomization. The time point for the primary endpoint has been defined to minimize the risk of missing data.

For the primary endpoint, a secondary analysis will be performed per protocol, including patients with the endpoint assessment, and for whom the strategy allocated during randomization was fully implemented (ie, patients allocated to the foot reflexology group that did not receive four sessions of foot reflexology will be excluded from the analysis).

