In 2018, in both sexes combined, lung cancer was the leading global cause of cancer death (18.4%), followed by digestive system cancer including colorectal (9.2%), stomach (8.2%), and liver (8.2%) [21]. According to national and international recommendations, adjuvant treatment for lung and digestive system cancer is platinum-based chemotherapy [22-26]. Anticancer therapy cisplatin has a high emetic risk (incidence of CINV >90%), while carboplatin and oxaliplatin have a moderate emetic risk (incidence of CINV is from 30% to 90%) [17].

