## Methods

### Trial Design

An open-label randomized controlled trial (RCT) will be carried out, in which patients are randomized to one of two groups at a 1:1 ratio: (1) conventional care with foot reflexology (40 patients) and (2) conventional care without foot reflexology (40 patients). Randomization is stratified on the type of cancer (digestive system or lung) and the presence or absence of metastases. The sponsor is the Hospices Civils de Lyon. The principal investigator is [name]. To design this trial, we used the CONSORT Statement for Randomized Trials of Nonpharmacologic Treatments [27].

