### Eligibility Criteria of Participants

Eligibility requirements for this study are the following: patients aged ≥18 years; patients with lung cancer (eg, non–small cell lung carcinomas, small cell lung cancer, mesothelioma) or digestive system cancer (eg, colorectal cancer, pancreatic cancer, liver cancer); patients on platinum-based chemotherapy with or without radiation therapy concomitant (eg, digestive system cancer: FOLFOX, FOLFIRINOX, GEMOX, LV5FU2-CDDP; lung cancer: cisplatin-vinorelbine, pemetrexed-cisplatin, pemetrexed-carboplatin, carboplatin-paclitaxel); World Health Organization performance status ≤2; patients affiliated to the national social security system or equivalent; patients able to complete the questionnaires (comprehension of oral and written French language); and patients who provide written informed consent. The exclusion criteria are phlebitis; vena cava syndrome; weight loss >5% in the 3 months before inclusion date; uncontrolled pain; patients receiving morphine or morphine derivatives; brain metastases; patients receiving foot reflexology outside the study; patients under guardianship or curatorship or who have been deprived of their rights. All data will be collected from outpatients and inpatients.

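### Platinum agent, the only determinant of nausea and vomiting that the protocol quantifies, is in none of the three nausea and antiemetic models; adding it is a cheap gain in precision

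*Protocol article*

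**What the plan says.** All references are to the protocol article.

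- **Background** names the emetogenicity of the chemotherapy among the determinants of nausea and vomiting, and then gives figures for the platinum agents: "Anticancer therapy cisplatin has a high emetic risk (incidence of CINV >90%), while carboplatin and oxaliplatin have a moderate emetic risk", the latter put at 30% to 90%. No other determinant in the article has a figure.
- **Eligibility Criteria of Participants** lists examples for each cancer type. For lung these are two cisplatin and two carboplatin doublets: "lung cancer: cisplatin-vinorelbine, pemetrexed-cisplatin, pemetrexed-carboplatin, carboplatin-paclitaxel". The four digestive examples include FOLFOX and LV5FU2-CDDP, which I read as an oxaliplatin and a cisplatin regimen.
- **Trial Design**: "patients are randomized to one of two groups at a 1:1 ratio", stratified by cancer type and metastatic status.
- **Type of Statistical Analysis Used**: the primary comparison is a "linear model adjusted on the type of cancer (digestive system or lung) and the presence of metastases (randomization stratification factors"). The mixed Poisson model of episodes and the mixed logistic model of antiemetic use take group and the same strata as fixed effects. The section describes the primary estimate as adjusted for possible confounders.

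**The concern.** The article identifies a baseline factor that separates patients by their risk of the symptom under study. It admits patients from both sides of that divide within each cancer type, and then leaves the factor out of every model of the symptom. The covariate sets of all three models are stated, so this is a choice on the page and not a detail left for later.

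Two things are at stake. Variation between the emetic classes that cancer type does not absorb stays in the error term and widens the intervals. And with 40 patients per group the arms may differ by chance in their share of cisplatin patients. If that is noticed only at analysis, in an open-label trial, adjusting for it then would look driven by the data.

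**Working it through.** **1. The plan's own figure.** From Sample Size: the improvement "was 49.5% in the placebo group, and 73.5% in the massage group", a difference of 73.5 − 49.5 = 24 points, "with a common standard deviation of 32.2"%, "for a two-sided risk of 5"%, and 40 per group "to demonstrate a statistically significant difference between the two groups with a power of 90"%.

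n per group = 2 × (1.96 + 1.2816)² × 32.2² / 24² = 37.8, so 38. The noncentral t gives 39, and dividing 38 by the Wilcoxon efficiency 3/π gives 39.8, so 40. The stated 40 reproduces.

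At 40 per group the standard error is 32.2 × √(2/40) = 7.20. Power is Φ(24/7.20 − 1.96) = 91.5% (90.9% by the noncentral t). The calculation takes no credit for covariates, so leaving the agent out does not undermine it.

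**2. What adjustment could add to the primary comparison.** Let R² be the share of outcome variance that the agent explains. The documents do not give it, so a range is assumed. The residual SD is 32.2 × √(1 − R²).

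| Assumed R² | SD | 95% half-width at 40 per group | Power at 40 (normal) | n per group for 90% |
|---|---|---|---|---|
| 0 | 32.2 | 14.1 | 91.5% | 38 |
| 0.02 | 31.9 | 14.0 | 92.0% | 38 |
| 0.05 | 31.4 | 13.8 | 92.8% | 36 |
| 0.10 | 30.6 | 13.4 | 94.0% | 35 |
| 0.20 | 28.8 | 12.6 | 96.1% | 31 |

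The gain is 0.5 to 4.6 percentage points of power. To see what these values imply, let p be the cisplatin share and g the gap between classes in mean outcome, so that R² = p(1 − p)g²/32.2². With p = 0.3, a gap of 10 points gives 0.02 and a gap of 20 points gives 0.08. With p = 0.5, R² = 0.20 needs g = √(0.20 × 32.2²/0.25) = 28.8 points, more than the planned treatment effect of 24. The last row is therefore a generous upper end.

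**3. Chance imbalance.** With two independent Binomial(40, p) counts and p assumed at 0.2 to 0.5, the arms differ in cisplatin share by at least 10 points with probability 0.33 to 0.43, and by at least 20 points with probability 0.04 to 0.09. These figures ignore stratification and so are upper values. If a 20-point imbalance met a gap of 10 to 20 points between classes, the estimate would move by 0.20 × 10 = 2 to 0.20 × 20 = 4 points, in either direction. That is 0.28 to 0.56 of the standard error of 7.20.

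**4. Does cancer type already stand in for the agent?** In part. Assume equal strata, with cisplatin shares p_L of 30% to 70% in lung and p_D of 5% to 20% in digestive cancer. The fraction of the variance in agent left after cancer type is [0.5 p_L(1 − p_L) + 0.5 p_D(1 − p_D)] / [p(1 − p)], where p is the mean of p_L and p_D. For 50% and 5% this is 0.149/0.199 = 0.75. Over the four combinations tried it runs from 0.55 to 0.90.

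**5. How direct the link is.** The Background figures are incidences of nausea and vomiting. The Poisson model counts episodes between cycles, and the logistic model concerns antiemetics taken over the cycles, so the agent bears on both directly. The primary outcome is a relative change in the visual analogue scale between arrival and a later point in the same cycle-2 visit. Nothing in the article shows that the agent predicts that change.

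**The case against.** Adjusting for the randomisation strata is the standard match of analysis to design. That is reason enough for metastatic status to be in the models, whether or not it predicts nausea. A further prognostic covariate is optional. The Background section lists emetogenicity alongside age, gender, alcohol use, motion sickness and other factors without ranking them, and the two incidence bands adjoin, so they do not fix the gap between agents. The cisplatin share and the effect of agent on the outcome have no source in the documents. All of this stands. It limits the point to an improvement, with a size that can only be shown as a range.

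A reader might go further in three ways that the documents do not support:

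- **The treatment comparison is confounded by agent.** It is not. Allocation is random, imbalance falls either way, and the confidence interval already allows for it.
- **The trial is underpowered for this reason.** It is not. The planned number reproduces with an SD that assumes no help from covariates.
- **Agent is the strongest predictor of the outcome.** The article says only that agents differ in incidence. It is the one determinant with figures, which is a weaker statement.

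What does not stand is that this can be left to a fuller document. The covariates are listed for each model, and the one determinant with figures is not among them.

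**Conclusion.** A cheap improvement, not an error. The three models adjust for cancer type and metastases only, while the article's own figures separate cisplatin from the other two agents and both classes occur within each cancer type. The consequence is some loss of precision and exposure to chance imbalance. Type I error and the stated 90% power are unaffected.

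The case is firmest for the episode and antiemetic models, although the documents give no figures from which to compute the gain there. For the primary model the gain of 0.5 to 4.6 points of power rests wholly on the assumed R² of 0.02 to 0.20. The imbalance figures rest on an assumed cisplatin share of 20% to 50% and take no account of stratification.

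**What to change.** Before the data are analysed, prespecify the planned platinum agent (cisplatin versus carboplatin or oxaliplatin), as recorded before randomisation, as an additional fixed effect:

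- in the mixed Poisson model of episodes and the mixed logistic model of antiemetic use;
- in the primary linear model, stating that the gain there is expected but not established.

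Use the agent planned at randomisation, not the one later given, so that it remains a baseline variable. Keep the van Elteren fallback stratified on the two randomisation factors only. A third factor would make up to 2 × 2 × 2 = 8 strata in 80 patients, and a rule that depended on cell sizes would add freedom to the primary test.

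Randomisation and sample size do not change. The cost is a sentence in the analysis plan and one degree of freedom per model. The planned regimen is known at enrolment because platinum-based chemotherapy is an eligibility condition and allocation precedes treatment. The digestive stratum may hold few cisplatin patients, so the agent should enter as a main effect without an interaction with cancer type.

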### Evaluation Criteria

#### Primary Outcome

The primary outcome is the relative change in the severity of nausea and vomiting, as assessed with a visual analogue scale (VAS). The patient is asked to mark their current nausea level on the horizontal line with anchor statements on the left (a happy face, no nausea=0 mm) and on the right (a very sick green face, paroxysm of nausea or vomiting=100 mm). Unlike vomiting, which is measurable by the number of episodes per day, nausea is a subjective experience. For that reason, we will use a VAS to evaluate the severity of nausea in patients [30]. For patients in the intervention group, this measurement will be done when the patient arrives at the outpatient or inpatient department and after the foot reflexology session, during the second cycle of chemotherapy. For patients in the control group, this measurement will be done when the patient arrives at the outpatient or inpatient department and before leaving the hospital, during the second cycle of chemotherapy. The assessment is performed by a nurse or clinical research assistant.

All patients will continue to receive standard antiemetic drugs (eg, 5-hydroxytryptamine 3 receptor antagonists, dexamethasone, and neurokinin-1 inhibitor receptor antagonists). According to chemotherapy protocols, oral antiemetic agents are included, and patients are instructed to complete the course.

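### The primary analysis may transform the VAS score or switch to a van Elteren test, and neither route yields the difference in mean relative change that the trial promises and is sized on

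*Protocol article*

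**What the plan says.** Under Primary Outcome, the protocol article defines the endpoint on a percentage scale: "The primary outcome is the relative change in the severity of nausea and vomiting, as assessed with a visual analogue scale (VAS"). The scale's lower anchor is zero ("a happy face, no nausea=0 mm").

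The Sample Size section uses the same scale. It takes from an earlier massage study that "the mean improvement for CINV (measured using a VAS) was 49.5% in the placebo group, and 73.5% in the massage group", with a common SD of 32.2%, and arrives at 40 patients per group for 90% power at a two-sided 5% level.

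The section Type of Statistical Analysis Used then makes these statements about the primary endpoint, in this order:

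- The analysis: "comparison of the relative change in the VAS between the two groups will be performed using a linear model adjusted on the type of cancer" and on the presence of metastases.
- What it delivers: "This model allows the estimation of the difference in mean relative variation of VAS between the two groups", with a 95% confidence interval.
- The first escape: "The VAS score may be transformed satisfy the assumptions of the linear model".
- The second escape: "If the assumptions of the model cannot be verified, the comparison between the two groups will be done using the van Elteren test".
- Subgroups: "Specific estimates of the difference in relative VAS variation between the groups will be provided for both types of cancer, and by metastatic status".

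The article does not name the transformation, say whether it is applied before or after the relative change is formed, or say how a result would be brought back to the percentage scale.

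**The concern.** The endpoint, the sample size, the promised estimate and the subgroup estimates are all expressed as relative change in the VAS as measured. The two escapes leave that scale.

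Relative change is not preserved when the score is transformed non-linearly: the percentage fall in the square root or logarithm of a score is not the percentage fall in the score. A model fitted to the former estimates something else. If the authors meant to transform the relative change itself, the coefficient is a difference on the transformed scale and still not a difference in mean relative change. The van Elteren test is a stratified rank test, so it gives a p-value and no difference in means.

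If either escape is used, the trial could report a primary result without the estimate and confidence interval it set out to provide, and the result could not be set against the 24-point difference it was sized to detect.

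**Working it through.** **1. The plan's own figure.** Inputs from Sample Size: difference 73.5 − 49.5 = 24 points, SD 32.2, two-sided 5%, power 90%.

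n per group = 2 × (1.960 + 1.282)² × (32.2/24)² = 37.8, so 38. The t-test version gives 38.8, so 39. With 40 per group the power is 91.5% (normal) or 90.9% (t). The stated 40 is reproduced, and nothing below changes it. It does confirm that the trial is sized on the untransformed percentage scale.

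**2. What a transformation of the score does to relative change.** Write the fall as 100 × [g(before) − g(after)] / g(before). The article names no g. I assume the square root and log(VAS+1); the +1 is needed because 0 mm is a permitted score.

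For a true 50% fall:

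| Before to after (mm) | Untransformed | Square root | log(VAS+1) |
|---|---|---|---|
| 80 to 40 | 50% | 29.3% | 15.5% |
| 40 to 20 | 50% | 29.3% | 18.0% |
| 20 to 10 | 50% | 29.3% | 21.2% |
| 10 to 5 | 50% | 29.3% | 25.3% |

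The square-root column is 1 − √0.5 = 0.293 at every starting value. The first log entry is 1 − log(41)/log(81) = 1 − 3.714/4.394 = 0.155.

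**3. What it does to the planned contrast.** Treat 49.5% and 73.5% as falls in single patients, for illustration.

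- Untransformed: 24.0 points.
- Square root: (1 − √0.265) − (1 − √0.505) = 48.5% − 28.9% = 19.6 points.
- log(VAS+1): 14.2 points from a start of 80 mm, 16.2 from 40 mm, 18.6 from 20 mm and 21.1 from 10 mm.

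**4. How likely the escapes are to be needed.** VAS cannot fall below 0, so improvement cannot exceed 100%. If the planned distributions were normal:

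- Reflexology: P(improvement > 100%) = 1 − Φ((100 − 73.5)/32.2) = 1 − Φ(0.823) = 20.5%.
- Control: 1 − Φ((100 − 49.5)/32.2) = 1 − Φ(1.568) = 5.8%.

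The planned mean and SD therefore imply a pile-up at the ceiling or a skewed distribution. I simulated 40 patients per arm from these two normal distributions, capped at 100%, and applied a Shapiro-Wilk test at 5% to the residuals from the group means. It rejected in about 58% of trials. The article states no criterion, so Shapiro-Wilk is my assumption.

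**5. Whether a transformation would help.** In the same simulation, with an assumed lognormal arrival VAS (median 30 mm, log-SD 0.5), the residuals failed Shapiro-Wilk in about 88% of trials for the relative change of the square-rooted score and in about 100% for log(VAS+1). Neither removes the pile-up at 100%. Followed literally, the plan would then often end at the van Elteren test, which gives no difference in means.

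**The case against.** **The wording may be loose.** The same section gives the Body Image Questionnaire a parallel sentence, and there the score is the outcome being modelled. By analogy, the VAS sentence may mean the modelled outcome, that is, the relative change. This is plausible, and on that reading equal percentage falls would receive equal scores. It does not rescue the estimate: a coefficient on a transformed relative change is still not the difference in means promised just before it.

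**An article leaves detail to the full protocol or SAP.** This is true of the choice of function, the trigger and any back-transformation, and I do not count their absence as a fault. For the same reason I do not claim that the choice would be made after seeing the data, since an unseen plan could fix the rule in advance. The conflict lies between printed sentences: one names the quantity to be estimated, and the next two allow analyses that do not estimate it.

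**The van Elteren test is a legitimate, stratified, pre-specified fallback.** As a test it is: nothing suggests that it would be applied to anything but the relative change, and in a simulation an unstratified rank test standing in for it held about 5% type I error. The objection is only that it supplies no estimate on the scale of the endpoint. The article still promises subgroup differences in relative change but does not say that the overall estimate would be kept.

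**Two stronger readings are tempting and not supported.** A reader might infer that patients with identical percentage falls would always be scored differently. That holds for log(VAS+1) and other transformations with an offset. It is false for the square root and any pure power, as the table shows.

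A reader might also infer that the clause inflates the false-positive rate. In simulation, inflation appeared only for log(VAS+1), and only with two- to five-fold differences between arms in median arrival VAS, which nothing in the article supports. With equal arrival scores the error stayed near 5%. That analysis also fails the residual check in about 100% of trials, so the plan's own rule would discard it for the van Elteren test.

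**Conclusion.** The point stands as a conflict over the primary estimate. The article promises a difference in mean relative change in VAS and then permits two routes that do not produce it. The shift in scale is material: 24 planned points become 19.6 under a square root, or 14.2 to 21.1 under log(VAS+1) for starts from 80 down to 10 mm. On the plan's own means and SD, the condition that opens these routes would be met in roughly 58% of trials.

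These sizes rest on assumptions: the two transformations, Shapiro-Wilk as the trigger, and normal distributions capped at 100%. The concern is conditional, because if no transformation is used and the linear model is kept, the promised quantity is estimated. The sample size is unaffected, and no inflation of type I error is shown. It should be corrected because it concerns the primary endpoint and the remedy is cheap.

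**What to change.** In Type of Statistical Analysis Used, and in the SAP:

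- Delete the option to transform the VAS score, or restrict any transformation to a labelled sensitivity analysis.
- State that the primary estimate is the difference in mean relative change on the untransformed VAS, from the linear model adjusted for cancer type and metastases, with a heteroscedasticity-robust (for example HC3) or bootstrap 95% confidence interval, reported whatever the residuals look like.
- Keep the van Elteren test as a named sensitivity analysis instead of a replacement.

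Other choices could also protect the estimate; what matters is that one is fixed and that the result is reported on the relative-change scale. The cost is a few sentences and a few lines of code. The downside is possibly slightly less power than a rank test if the endpoint is very skewed.

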## Discussion

According to a European survey reported by Molassiotis et al [1], 35.9% of patients with cancer use CAMs, and after a diagnosis of cancer the use of CAMs increases by at least 30%. For varied reasons, some patients do not inform caregivers or health care professionals that they use CAMs [37,38]; however, certain CAMs could have potential interactions with conventional cancer treatments [39,40]. In parallel, oncologists lack adequate information about the safety and efficacy of CAMs to confidently inform their patients [41-43] and they have requested more rigorous evaluation [42,43]. Moreover, the World Health Organization’s Traditional Medicine Strategy emphasizes the importance of thorough evaluation; the objectives of this strategic approach are to inform policy; determine safety, efficacy, and quality; increase access; and promote the rational use of traditional medicine [44].

This RCT (Clinicaltrials.gov identifier: NCT03508180), which began in June 2018, assesses the benefits of foot reflexology. The expected results are a decrease in CINV and anxiety, as well as an improvement in quality of life and self-esteem. This will also allow the investigation of any potential difference in benefit between patients with lung cancer and patients with digestive system cancer, and patients with different stages of cancer (metastatic and nonmetastatic). The results will be available in the last quarter of 2020.

This study does have limitations. First, the results may not be representative of all cancers; patient recruitment was only done at one cancer center. Even if conventional treatments are similar within the various private and public health care centers in France, a larger multicenter study would ensure that the results are generalizable.

In conclusion, the current management of patients with cancer involves treatment with conventional medicine while offering supportive oncological care. If the results of this study are significant, foot reflexology may be a promising complement to conventional antiemetic drugs.

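### The protocol says differences in benefit by cancer type and metastatic status can be investigated, but the stated analysis does not estimate those differences

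*Protocol article*

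**What the plan says.** Protocol article, Trial Design: 80 patients are randomized 1:1, stratified by cancer type (digestive system or lung) and by presence of metastases.

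Type of Statistical Analysis Used: the primary endpoint, relative change in the nausea VAS, is compared between groups with a linear model. The two stratification factors enter as adjustment variables, and the result is an adjusted mean difference with a 95% confidence interval. The van Elteren test is the fallback if the model assumptions fail. The section then adds: "Specific estimates of the difference in relative VAS variation between the groups will be provided for both types of cancer, and by metastatic status".

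Discussion: the use of these results is described as follows: "This will also allow the investigation of any potential difference in benefit between patients with lung cancer and patients with digestive system cancer". The same sentence extends this to patients with and without metastases.

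The article mentions no interaction term, heterogeneity test or direct comparison of the subgroup effects. It does not call the subgroup question exploratory and gives no rule for reading the subgroup estimates.

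**The concern.** The Discussion's question concerns a contrast between two treatment effects: is the benefit in lung cancer different from the benefit in digestive system cancer? The stated output is each effect on its own. The contrast, with its own standard error and interval, is not among the stated results, and the van Elteren fallback would not supply it either.

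When only subgroup estimates are reported, readers tend to compare them by asking which one is significant. In subgroups of about half the trial, one significant and one non-significant result is common even when the true benefit is the same in both. It could then be reported that reflexology works in one cancer and not in the other. This matters in a trial that aims to give oncologists evidence on which to base recommendations.

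**Working it through.** **Inputs** (Protocol article, Sample Size): mean improvement 49.5% and 73.5%, so a difference of 24.0 points; SD 32.2; two-sided 5%; power 90%; 40 per group. Subgroup sizes are not given, so the splits below are assumptions, shown as patients per arm in the two subgroups.

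**Reproducing the stated sample size.** n per group = 2 × (1.960 + 1.282)² × 32.2² / 24² = 37.8, so 38. The t-based calculation gives 39 (power 90.1%), and 40 per group gives 90.9%. The stated figure, "it is necessary to include 40 patients per group", is reproduced within rounding.

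**Power within one subgroup.** With n per arm, SE = 32.2 × √(2/n). For n = 20, SE = 10.18 and the noncentrality is 24 / 10.18 = 2.36. The noncentral t with 38 degrees of freedom gives power 63.2%.

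**Chance that exactly one of two subgroups is significant.** The two subgroups contain different patients, so the chance is p₁(1 − p₂) + p₂(1 − p₁). At 20/20 this is 2 × 0.632 × 0.368 = 0.465.

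**The contrast itself.** Interaction SE = 32.2 × √(2/n₁ + 2/n₂). At 20/20 this is 32.2 × √0.2 = 14.4 points. The 95% CI half-width (t, 76 degrees of freedom) is 1.992 × 14.4 = 28.7 points.

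With a true benefit of 24 points in both subgroups (columns 2 and 3), and for a true interaction of 24 points (column 5):

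| Split per arm | Subgroup power | Exactly one significant | Interaction SE | Power for a 24-point interaction | Interaction detectable with 80% power |
|---|---|---|---|---|---|
| 20/20 | 63% / 63% | 47% | 14.4 | 38% | 41 points |
| 24/16 | 71% / 53% | 49% | 14.7 | 36% | 42 points |
| 28/12 | 78% / 42% | 55% | 15.7 | 33% | 45 points |
| 30/10 | 81% / 35% | 59% | 16.6 | 30% | 47 points |

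**Dependence on the true effect** (20/20): with a common benefit of 18 points the chance of exactly one significant subgroup is 48%; with 12 points it is 33%; with no effect it is 2 × 0.05 × 0.95 = 9.5%.

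**Comparison.** When the benefit is equal in both subgroups, an interaction test at two-sided 5% declares a difference in 5% of trials per factor, whatever the size of the common benefit and whatever the split.

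**The case against.** The strongest reply is that the protocol does nothing wrong here. Reporting effects within pre-specified stratification factors is good practice. Such estimates can come from a linear model with a treatment-by-factor term, and the text does not rule one out. An analysis plan that is not shown may contain the test. The Discussion sentence is hedged, and subgroup benefit is not among the objectives or outcomes. With independent subgroups, a reader who is given intervals could work out the contrast.

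Much of this stands. A reader might infer that the protocol intends to judge differential benefit by separate subgroup p-values, or that it has excluded an interaction term. The document supports neither reading: it speaks of estimates, mentions no subgroup significance test and sets no decision rule. The 47% to 59% therefore describes what would follow from one particular way of reading the results, not a procedure in the plan. It also needs a real common effect near the planned one.

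What does not fall away is the gap between aim and output. The article states what will be provided for the subgroups and, separately, what question the trial will allow to be investigated, and the first does not directly answer the second. Nor would an interaction term in an unseen plan change the low precision of the contrast, which the Discussion does not acknowledge. Low power of the interaction test is no reason to leave it out: the wide interval shows how little the trial can say about differential benefit.

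**Conclusion.** The concern holds as a minor point. The Discussion presents differences in benefit by cancer type and metastatic status as something the trial can investigate, while the stated analysis stops at one treatment estimate per subgroup.

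If those estimates were compared by significance, a spurious difference would appear in roughly half of trials per factor under the planning assumptions, against 5% with a direct test. That size rests on three assumptions: this way of reading the estimates, a split between 20/20 and 30/10 per arm, and a true common benefit near 24 points. The direct contrast would itself be imprecise. At 20/20 its 95% CI reaches 28.7 points either side, more than the whole planned effect. The primary comparison and the sample size are unaffected.

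**What to change.** In Type of Statistical Analysis Used, add treatment-by-cancer-type and treatment-by-metastasis terms to the primary linear model, one at a time. Report each interaction estimate with its 95% CI beside the subgroup estimates. State that any conclusion about differential benefit will rest on these interaction estimates only, and not on whether individual subgroups reach significance. In the Discussion, describe the question as exploratory and mention the limited power.

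The cost is two extra model fits and a few sentences. No additional patients or data are needed and the primary analysis does not change. The only downside is a more modest subgroup claim.
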